### Objective 3: Prioritisation process

Once signals have been generated, our next objective will be to combine these signals with descriptive information on prescribing (objective 1), current available evidence, and workshop discussions with a multidisciplinary group of clinicians, epidemiologists, and patient and public involvement representatives. Information from the following domains will be considered when prioritising medications(Fig 2).

**Fig 2 pone.0349045.g002:**
[figure not shown]
Process for selecting medications for detailed analysis.

**Available evidence**

For all signals identified we will annotate them with information from the BNF, UKTIS, Reprotox, TOXBASE and DART. We will add information from searches on PubMed and Ovid.

Each individual medication-outcome pair will be annotated as

iknown harmful effectiiknown indication effect (association between the reason the medication is taken and the outcome)iiiunknown – limited evidence for specific pairivunknown – limited evidence for composite exposure (broad medication groupings) and/or composite outcome (grouping of specific outcomes)vunknown – no evidence

**Likelihood of biases and confounding (including confounding by indication)**

Information on whether the medication is available over the counter will also be included because this can result in bias due to misclassification of exposure. An initial assessment of likelihood of confounding by indication will be discussed with input from clinicians. We will check for frequency of co-medication. This will highlight any signals that may be due to confounding by co-medication if they are prescribed >50% of the time with a medication that has a known effect on the relevant outcome.

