**Methods:**

We will describe trends in primary care prescribing in pregnancy over time, and socio-demographic patterning of prescribing, using data from pregnancies in the Clinical Practice Research Datalink (CPRD). We will identify and categorise maternal, fetal, and infant adverse outcomes reported in the CPRD and linked hospital and mortality data. We will use Bayesian signal detection models to analyse all medication/outcome pairs to identify where an outcome occurs significantly more frequently in mothers prescribed a specific medication than in mothers not prescribed it. Potential confounders will not be accounted for at this stage. Published evidence on the identified medication/outcome pairs will be reviewed and incorporated with the results from trends and signal detection analyses. These data will be used by Patient Involvement and Study Advisory Board workshops to prioritise medications for further research, with medications more commonly prescribed for underserved groups being given precedence. For three prioritised signals, cohort analyses will compare the occurrence of adverse outcomes in those prescribed compared to those not prescribed the medication of interest, adjusting for maternal morbidity, co-medications, and other measured confounders.

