### Objective 2: Signal detection

Adverse outcomes will be defined as above. Exposures will be prescriptions of individual active ingredients of medications. The estimated dates of pregnancy will be used to identify any medications prescribed in the three months prior to pregnancy or during pregnancy, and analyses will be run for each trimester separately as well as for the three-month period prior to pregnancy.

We will apply standard Bayesian signal detection models using the Information Component (IC) [24–26]. This method is based on comparing the frequency of occurrence of the outcome of interest in mothers prescribed the medication of interest compared to the frequency of occurrence of the outcome of interest in mothers not prescribed the medication of interest for each medication/outcome pair. IC values that are positive indicate that the outcome and prescribed medication occur more frequently together than would be expected due to chance if both events were independent. In brief the observed counts (a,b,c,d from a two-by-two table) are assumed to have a Multinomial distribution (pa,pb,pc,pd,n). With a Dirichlet prior distribution for pa pb pc and pd the corresponding posterior distribution is also a Dirichlet distribution. Assuming an uninformative prior likelihood, 100,000 random samples from the proposed posterior Dirichlet distribution can be generated and the median IC with its 95% credible intervals obtained [27]. Pairs with a positive lower 95% credible interval have sufficient evidence that they are occurring more frequently than would be expected due to chance and are classified as signals.

Our new method of hierarchical modelling will then use these results to identify groups in the data using bi-clustering techniques. For this method, pairs with a positive lower 90% credible interval using the IC are considered ‘potential signals’. A group is defined as containing all medication/outcome pairs where all medications in the group have a potential signal with the same outcomes in the group. Medications with similar pharmacological properties are likely to be in the same groups, but the actual group membership is determined purely by the data. These groups will then be used to calculate an observed to expected ratio, adjusted for groupings, for each medication/outcome pair.

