**Prevalence of use overall and in under-represented groups**

Commonly prescribed medications will be given priority over those prescribed more infrequently. We will also be able to identify any medications prescribed more frequently in under-represented socio-demographic groups from our results in objective 1, which will be an additional priority criterion.

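### The >50% co-prescribing rule, the only numeric confounding check before prioritisation, ignores co-medication use in pregnancies not prescribed the medication and the size of the co-medication's effect

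*Protocol article*

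**What the plan says.** The screen is unadjusted by design. The abstract says "Potential confounders will not be accounted for at this stage". Under Objective 2, each medication/outcome pair is reduced to a crude table: "In brief the observed counts (a,b,c,d from a two-by-two table) are assumed to have a Multinomial distribution". The signal rule is "Pairs with a positive lower 95% credible interval have sufficient evidence that they are occurring more frequently than would be expected due to chance". The hierarchical step brings in no covariates; its only adjustment is for groups found in the data: "These groups will then be used to calculate an observed to expected ratio, adjusted for groupings, for each medication/outcome pair".

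Confounding is taken up in Objective 3. The available-evidence annotation has a category for associations explained by the indication. The domain on biases and confounding then adds two checks. One is qualitative: "An initial assessment of likelihood of confounding by indication will be discussed with input from clinicians". The other is numeric and concerns co-medication: "This will highlight any signals that may be due to confounding by co-medication if they are prescribed >50% of the time with a medication". It applies only where the co-medication is one "that has a known effect on the relevant outcome". The same domain also records over-the-counter availability, but as a source of exposure misclassification.

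The rule as stated contains no comparison with pregnancies not prescribed the medication and no threshold for how large the known effect must be.

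**The concern.** A co-medication confounds a crude comparison only if it is used to a different extent in the two groups being compared and also affects the outcome. A cut-off on its use among the prescribed alone cannot tell a large imbalance from none. It can therefore err both ways: below 50% it is silent on signals that a co-medication could fully explain, and above 50% it marks signals that the co-medication cannot explain.

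This matters because only three signals go on to an adjusted cohort analysis. The Discussion presents the longer prioritised list as a product in its own right. For medications on that list but outside the three, this rule is the only quantitative guard against confounding that the article states.

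**Working it through.** **Inputs.** The article gives the 50% cut-off without a derivation, so there is no figure to reproduce. It gives no co-prescribing rates, effect sizes, outcome risks or cohort size; all such values below are assumptions, shown over a range.

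**Formula.** Let the medication have no effect on the outcome. Let p1 and p0 be the proportions of prescribed and not-prescribed pregnancies that receive the co-medication, and RR its effect on the outcome. The crude risk ratio for the medication is then pure bias:

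B = [1 + p1(RR − 1)] / [1 + p0(RR − 1)]

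The 50% rule, read per pregnancy, looks at p1 only.

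| p1 | p0 | RR | B | Highlighted by the rule? |
|---|---|---|---|---|
| 30% | 5% | 2 | 1.30/1.05 = 1.24 | no |
| 30% | 5% | 3 | 1.60/1.10 = 1.45 | no |
| 49% | 5% | 2 | 1.49/1.05 = 1.42 | no |
| 45% | 2% | 4 | 2.35/1.06 = 2.2 | no |
| 60% | 60% | 3 | 2.20/2.20 = 1.00 | yes |
| 55% | 50% | 2 | 1.55/1.50 = 1.03 | yes |
| 60% | 5% | 1.1 | 1.06/1.005 = 1.05 | yes |

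The four cases that go unhighlighted carry more bias than the three that are highlighted. Moving the cut-off does not help, because the ordering by p1 is not the ordering by B.

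**Largest bias the rule lets through.** With p1 = 50% and p0 = 0, B = 1 + 0.5(RR − 1). This is 1.25, 1.5, 2.0 and 3.0 for RR = 1.5, 2, 3 and 5.

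**Would such pairs become signals?** The IC was computed as the article describes, from 100,000 Dirichlet draws on the expected two-by-two table, with an assumed prior of 1 in each cell. Assume 500,000 pregnancies and p0 = 5%.

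With 2% prescribed the medication and an outcome risk of 5% without the co-medication:
- p1 = 30%, RR 2: IC 0.30 (95% credible interval 0.20 to 0.41)
- p1 = 30%, RR 3: IC 0.53 (0.43 to 0.62)
- p1 = 49%, RR 2: IC 0.49 (0.40 to 0.59)

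All three are signals for a medication with no effect, and none is highlighted.

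With 0.1% prescribed and an outcome risk of 1%, the lower limits of the same three cases are −0.75, −0.41 and −0.49, so none is a signal. The problem thus falls mainly on commoner medications and outcomes, and commonly prescribed medications are the ones that Objective 3 ranks higher.

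**What restriction does.** In the first case, 10,000 pregnancies are prescribed the medication and 70% of them, 7,000, do not have the co-medication. The outcome risk among them is 5%, the same as in not-prescribed pregnancies without it, so the recomputed IC centres on zero.

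**The case against.** The strongest reply is that the rule only highlights signals for discussion and excludes nothing. Over-highlighting costs a conversation. The second condition, a known effect on the outcome, narrows it further: the case of 60% in both groups needs a harmful medication used in most pregnancies, and nothing in the article suggests that one exists. This stands, and it makes missed confounding below 50% the more important half of the point.

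It is also fair that every signal is annotated for indication effects, that clinicians discuss confounding by indication, and that Objective 1 results, a patient workshop and an advisory board workshop all come before the list. A reader might infer that confounded pairs reach the list unflagged. The article does not show that. They can pass this check; other review may still catch them.

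Three further inferences are tempting and not supported:

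- *That the crude screen is itself an error.* It is openly declared, and the Limitations section treats signals as hypotheses and admits spurious associations.
- *That medicines used more in disadvantaged groups gain a confounded signal and then extra priority for the same reason.* The article lists "medications prescribed more frequently in under-represented socio-demographic groups from our results in objective 1, which will be an additional priority criterion", which is an equity criterion. It does not say that these groups have higher outcome risks.
- *That the screen must be stratified by calendar period, age and deprivation.* Drift over 20 years can produce a signal. With two equal halves of 500,000 pregnancies, prescribing rising from 1% to 2% and the outcome from 3% to 6% gives IC 0.15 (0.01 to 0.29). Milder drift (1% to 1.5%, 4% to 5%) gives 0.035 (−0.13 to 0.19), no signal. Stratified expected counts also do not fit directly into the stated two-by-two Dirichlet model. This is a design choice open to debate.

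**Conclusion.** The point holds for the co-medication rule. Its cut-off is placed on a quantity that does not determine confounding. Under plausible but assumed inputs it leaves spurious ratios of 1.24 to 2.2 unhighlighted while highlighting a pair with a ratio of 1.00. The direction of the argument follows from the formula and needs no assumed value; the sizes do. Whether a biased pair also becomes a signal depends on how common the medication and the outcome are. How many signals are affected cannot be judged from the article, and the later qualitative review may reduce the number. The rule should be changed, but its weakness does not invalidate the screen.

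**What to change.** Drop the 50% cut-off. For each signal, tabulate the prevalence of every co-medication with a known effect on that outcome, in prescribed and in not-prescribed pregnancies. Where it is higher in the prescribed, recompute the IC in pregnancies without that co-medication and report it beside the crude IC in the workshop material. Where the literature gives a relative risk or a plausible range for the co-medication, B can be reported instead.

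The comparison and the restricted IC use only data already held. B needs an outside effect size that the study does not extract, so it should be the alternative and not the default.

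The cost is some extra analysis, for signals only, and wider intervals for rarely prescribed medications. With 0.1% of 500,000 pregnancies prescribed and p1 = 30%, 350 of 500 prescribed pregnancies remain, with 3.5 expected outcomes at a 1% risk. The restricted IC deals with the named co-medication only; confounding by indication still needs the clinical review.

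A period- and age-stratified IC for the signals taken to the workshop would be a useful optional sensitivity analysis. It is not needed to correct an error.

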**Prevalence of use overall and in under-represented groups**

Commonly prescribed medications will be given priority over those prescribed more infrequently. We will also be able to identify any medications prescribed more frequently in under-represented socio-demographic groups from our results in objective 1, which will be an additional priority criterion.

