## Statistical analysis

### Objective 1: Descriptive analysis

Individual medications will be grouped into summary categories broadly based on BNF chapter and section (S1 Table) [23]. Binary variables will be created for whether a medication from each of the categories was prescribed at any time during the pregnancy, each trimester of pregnancy individually, and for the three-month period prior to the start of pregnancy. Rates of prescribing of each medication category will be calculated per 1000 pregnancies.

To look at trends over time, rates of prescribing will be calculated for each year separately, with a pregnancy assigned to a single year based on the start date of the pregnancy.

Factors influencing the prevalence of prescribing of medication groups during pregnancy will be investigated by modelling whether a prescription was issued for a given medication group during pregnancy, using multivariable logistic regression models including variables such as maternal age, ethnicity, geographical region, deprivation, and comorbidities.

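### The criterion on under-represented groups is to be read from Objective 1, which analyses BNF-based categories, although the signals being prioritised are individual active ingredients

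*Protocol article*

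**What the plan says.** Four places in the protocol article bear on this.

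- **Objective 1: Descriptive analysis** sets the unit: "Individual medications will be grouped into summary categories broadly based on BNF chapter and section". The exposure variables follow it: "Binary variables will be created for whether a medication from each of the categories was prescribed at any time during the pregnancy", with matching variables for each trimester and for the three months before pregnancy. So do the rates: "Rates of prescribing of each medication category will be calculated per 1000 pregnancies". The one split of these rates that is stated is by year of pregnancy start. Factors influencing prescribing are studied by modelling whether a given medication group was prescribed, "using multivariable logistic regression models including variables such as maternal age, ethnicity, geographical region, deprivation, and comorbidities".
- **Objective 2: Signal detection** sets a different unit: "Exposures will be prescriptions of individual active ingredients of medications".
- **Objective 3, Prevalence of use overall and in under-represented groups** names the source of the criterion: "We will also be able to identify any medications prescribed more frequently in under-represented socio-demographic groups from our results in objective 1". It makes this an additional priority criterion, after stating that commonly prescribed medicines come before less common ones.
- **Abstract, Methods** describes the prioritisation as done "with medications more commonly prescribed for underserved groups being given precedence".

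**The concern.** The item being prioritised is a signalled ingredient, and the evidence named for the equity criterion is a result for the category that contains it. The article fixes both units and links them by naming Objective 1 as the source, but describes no step that bridges them. No section describes ingredient-level prescribing by socio-demographic group.

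A second, softer issue concerns adjustment. Being prescribed a medicine more frequently is a statement about frequency. If a group receives a medicine more often because it has more of the condition being treated, a coefficient conditional on that condition removes some or all of the excess.

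At stake is the quality of what reaches the two workshops. The criterion is the stated route by which use in underserved groups bears on which three medicines go forward to cohort studies.

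**Working it through.** The article gives no figure on this point, so there is none to reproduce. The units come from the text. All rates below are assumptions, chosen to show direction and rough size.

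**Units side by side**

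| Step | Unit | Split by socio-demographic group |
|---|---|---|
| Objective 1 rates | category | not stated (year only) |
| Objective 1 model | category | yes, with comorbidities listed as covariates |
| Objective 2 signals | active ingredient | none |
| Objective 3 criterion | medication, read from Objective 1 | required |

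The last row needs an ingredient-by-group quantity, and no row above it supplies one.

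**Dilution.** Let w be the ingredient's share of category prescribing in the comparison group and r its rate ratio in the group of interest. If all other ingredients have ratio 1 and no pregnancy receives two ingredients from the category, the category ratio is (1 − w) + w × r. With r = 2:

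- w = 5%: 0.95 + 0.05 × 2 = 1.05
- w = 10%: 0.90 + 0.10 × 2 = 1.10
- w = 20%: 0.80 + 0.20 × 2 = 1.20

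**Hiding and wrong credit.** Take a category with two non-overlapping ingredients, A and B, with rates per 1000 in the group of interest against the comparison group.

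- A 20 v 10 and B 80 v 90: the category is 100 v 100. A's odds ratio is (20/980)/(10/990) = 2.02; the category's is 1.00. A's excess is hidden.
- A 20 v 10 and B 60 v 90: the category is 80 v 100, odds ratio (80/920)/(100/900) = 0.78. The direction is reversed for A.
- A 10 v 10 and B 120 v 90: the category is 130 v 100, odds ratio (130/870)/(100/900) = 1.34. A is credited with an excess it does not have.

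**Adjustment (secondary).** Let c be the prevalence of a comorbidity, and p1 and p0 the probability of prescribing with and without it, the same in both groups. The group rate is c × p1 + (1 − c) × p0. With p1 = 50% and p0 = 2%:

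- c = 20%: 0.20 × 0.50 + 0.80 × 0.02 = 0.116, or 116 per 1000
- c = 10%: 0.10 × 0.50 + 0.90 × 0.02 = 0.068, or 68 per 1000

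The crude ratio is 116/68 = 1.71. Within each comorbidity stratum the groups have equal prescribing, so the adjusted odds ratio is 1.00. In nine other scenarios (c of 10–20% against 5–10%, p1 of 30–50%, p0 of 1–5%) the crude ratio ran from 1.31 to 2.42 with the adjusted odds ratio at 1.00 throughout. This is the extreme case, because prescribing depends on nothing but the measured comorbidity.

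**The case against.** The strongest reply is that this is a condensed article. The objectives promise to examine variation by age, ethnicity, socio-economic status, region and comorbidities, and the abstract promises socio-demographic patterning. Crude rates by group are routine beside such a model and may sit in the full protocol. The covariate list is open-ended, so the adjustment set is not fixed. The Introduction also gives the descriptive work the purpose of exposing sources of bias and confounding, which a multivariable model serves. All of this stands, and it is why the adjustment issue is secondary. A reader might infer that group differences will be seen only through a comorbidity-adjusted model; the text does not say so.

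The reply is weaker on the units, because crude category rates are still not ingredient rates. S1 Table is not shown, so the coarseness of the categories is unknown, and a category holding one ingredient would be an exception.

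A reader might also infer that the study cannot show which ingredients are used more in these groups. That goes too far: all primary care prescriptions are extracted, ingredient exposures are built for Objective 2, and the socio-demographic covariates are defined. The limit lies in Objective 1 as described, not in the data.

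Nor do the documents support saying that a medicine would show no excess, lose its priority and so change the three medicines studied. The simple dilution figures show a reduced excess, complete masking needs an offsetting ingredient, and all inputs are assumed. The criterion is one input among five domains, discussed in two workshops with no score or cut-off stated.

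**Conclusion.** The point holds as a mismatch of units. Followed as written, the plan supplies category-level evidence for an ingredient-level choice, and that evidence can err in either direction. On assumed inputs, a doubled ingredient making up 5% to 20% of its category appears as a category ratio of 1.05 to 1.20, and offsetting use within the category can hide or reverse it. The true size depends on S1 Table and on actual prescribing, neither of which is available here.

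The adjustment issue holds only conditionally. The one between-group comparison described lists comorbidities and can understate the actual difference in frequency, but unadjusted comparisons may also be planned.

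The signal detection itself is unaffected. The consequence is possibly misleading input to the workshops on a declared criterion, which is worth correcting before prioritisation begins.

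**What to change.** For each signalled active ingredient, tabulate crude prescribing rates per 1000 pregnancies by ethnicity, deprivation quintile, region and age band, with unadjusted rate ratios and intervals. In the Objective 3 subsection on prevalence of use, state that these rates, and not the category-level adjusted odds ratios, inform the criterion. Add a matching sentence under Objective 1. Keep the category models there as the explanatory analysis.

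The cost is a set of extra tables from data already extracted and a sentence in each of two sections. The timeline leaves room: Objective 1 results are expected by summer 2026 and prioritisation by spring 2027. The drawback is small-cell suppression and wide intervals for rarely prescribed ingredients. Where a cell is suppressed, the workshop material should say so, so that a blank is not taken as evidence of no difference.
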